**Methods and analysis:**

This study is a non-inferiority randomized controlled trial (RCT). One hundred and twenty-eight participants with PSD will be randomly assigned (1:1) to the intervention group (Tuina + rTMS treatment) and the control group (cognitive behavior treatment). The primary efficacy outcome is the change from baseline to week 2 in Hamilton Depression Rating Scale (HAMD) and Functional Magnetic Resonance Imaging (fMRI). Secondary efficacy outcomes include other assessments of the Mini-Mental State Examination (MMSE), The modified Barthel index (MBI), The National Institutes of Health Stroke Scale(NIHSS), inflammatory factor (IL-6, IL – 17, TNF-*α*, IFN-*γ*, IL-4, IL-10), and Functional near-infrared spectroscopy (fNIRS). Efficacy and scale assessments will be conducted at 1 month and 3 months after the completion of treatment.

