#### Statistical analysis of functional magnetic resonance imaging

In this study, fMRI data will undergo preprocessing using SPM12, including slice-timing correction, head motion correction, spatial normalization to the Montreal Neurological Institute (MNI) space, and spatial smoothing with a 6-mm Gaussian kernel. Functional brain networks will be constructed using both seed-based functional connectivity and ICA. For seed-based connectivity, regions of interest (ROIs) will be defined using the Automated Anatomical Labeling (AAL) atlas, and the mean BOLD signal from each ROI will be correlated to generate a connectivity matrix. Group ICA will be conducted using the GIFT software, decomposing the BOLD data into spatially independent components (ICs) that will be matched to canonical brain networks such as the default mode network (DMN), salience network (SN), and frontoparietal network (FPN). Additionally, graph-theoretical metrics, including degree centrality, clustering coefficient, and small-worldness, will be calculated to assess network efficiency and integration. Statistical analyses will involve comparing connectivity strength, network properties, and regional activations between groups using paired or independent t-tests, with corrections for multiple comparisons. Correlations between connectivity measures and clinical outcomes, such as HAMD scores, will be examined using Pearson or Spearman correlation coefficients. This comprehensive approach ensures robust exploration of functional brain networks and their clinical relevance.

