#### Statistical analysis of functional magnetic resonance imaging

Image data analysis is performed using Network Based Statistics (NBS) V1.2 statistical software based on MATLAB platform to construct local brain functional networks for two groups of subjects. Brain network features within each group are constructed through single sample *t*-test. The network between the observation group and the control group before and after treatment is compared using a two independent sample *t*-test; Multiple comparisons between local brain functional networks are corrected for false discovery rate (FDR). The difference is considered statistically significant with *p* < 0.05. The results of brain function data are presented using BrainNet Viewer 1.6 software. The significant brain regions detected before and after treatment are compared between the control group and the observation group. SPSS 25.0 software is used to perform correlation analysis with clinical scale scores. Pearson correlation is selected for normal distribution, while Spearman correlation is selected for non-normally distributed data. *p* < 0.05 is considered statistically significant. The results of the relevant analysis data are presented using the statistical parameter graph software Origin 2021.

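### Brain–scale correlations are tested at an unadjusted 0.05, although the imaging comparisons beside them are corrected for multiplicity

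*Protocol article*

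**What the plan says.** The protocol article has two sections headed Statistical analysis of functional magnetic resonance imaging.

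The second states "Multiple comparisons between local brain functional networks are corrected for false discovery rate (FDR"). It then says "The significant brain regions detected before and after treatment are compared between the control group and the observation group", and goes straight on to "SPSS 25.0 software is used to perform correlation analysis with clinical scale scores". The decision rule for that step is "Pearson correlation is selected for normal distribution, while Spearman correlation is selected for non-normally distributed data. *p* < 0.05 is considered statistically significant". No adjustment is attached to it.

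The first section is built the same way. Group comparisons of connectivity, network properties and activation are made "using paired or independent t-tests, with corrections for multiple comparisons". The following sentence reads "Correlations between connectivity measures and clinical outcomes, such as HAMD scores, will be examined using Pearson or Spearman correlation coefficients" and mentions no correction. Candidate regions come from an atlas: "regions of interest (ROIs) will be defined using the Automated Anatomical Labeling (AAL) atlas".

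Neither section names a leading region–scale pair or limits the regions, scales or time points. Neither says whether the arms are combined, or whether levels or changes are correlated. Four clinical scales are collected: HAMD-17, MMSE, MBI and NIHSS.

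**The concern.** Two families of imaging tests stand side by side. One is corrected; the other has a plain per-test 0.05 and an open-ended number of tests. A reader who sees FDR mentioned could assume that it covers the correlations too. As written, it does not.

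These correlations are the only stated analysis that ties the imaging to symptoms. Resting-state fMRI is named as the second primary outcome, and the Introduction gives imaging the task of explaining mechanism. A chance correlation could therefore be given more weight than it deserves.

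A second exposure depends on something the article leaves open. If patients from both arms go into one correlation, treatment can act as a common cause of the brain measure and the score. The two would then correlate even if there were no association among patients on the same treatment.

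**Working it through.** **Inputs from the article.** Per-test level 0.05. Four candidate scales. Planning difference 2.5 points and SD 4.49 (Sample size calculation). 51 per group before dropout allowance, so 102 in all.

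**Assumed, because the article gives no figure.** 1 to 20 regions carried into the correlations; one time point; a region difference between arms of 0.5–0.8 SD.

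**1. The plan's own figure.** n = (1.96 + 0.84)² × 2 × 4.49² / 2.5² = 50.58, rounded up to 51 per group; 51/0.8 = 63.75, rounded up to 64. Both reproduce. They do not bear on the multiplicity point, but they supply the 102 patients and the difference of 2.5/4.49 = 0.56 SD used in step 3.

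**2. Multiplicity.** For m independent tests with no true association, P(at least one false link) = 1 − 0.95^m. The expected number of false links is 0.05m.

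| Regions | HAMD only: m | P(≥1 false) | Four scales: m | P(≥1 false) | Expected false (four scales) |
|---|---|---|---|---|---|
| 1 | 1 | 5.0% | 4 | 18.5% | 0.2 |
| 3 | 3 | 14.3% | 12 | 46.0% | 0.6 |
| 5 | 5 | 22.6% | 20 | 64.2% | 1 |
| 10 | 10 | 40.1% | 40 | 87.1% | 2 |
| 20 | 20 | 64.2% | 80 | 98.3% | 4 |

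Positive correlation among regions or scales lowers the probabilities. It does not change the expected counts, because an expectation adds up whether or not the tests are independent. For scale, a Bonferroni threshold would be 0.05/12 = 0.0042 at 12 tests and 0.05/40 = 0.00125 at 40.

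**3. Pooled arms.** Suppose a region differs by d1 SD and the score by d2 SD between two equal arms, with no association within either arm. The pooled correlation is

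r = (d1·d2/4) / √[(1 + d1²/4)(1 + d2²/4)].

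With d2 = 0.557:
- d1 = 0.5: r = 0.0696/1.070 = 0.065
- d1 = 0.8: r = 0.1114/1.118 = 0.100

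By Fisher's z with n = 102 (standard error 1/√99), a two-sided 0.05 test rejects in 9.9% and 16.9% of trials respectively.

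**4. Does the selection of regions matter?** This was simulated with 51 per arm and 90 regions (an assumed number), of which 10 differ between arms by 0.6 or 0.8 SD. Regions were selected by Benjamini–Hochberg at 0.05, and there was no within-arm association with HAMD.
- Correlation within arm: per-test rejection 4.9–5.3% in every scenario.
- Arms pooled, no HAMD difference: 5.2–5.3%.
- Arms pooled, HAMD difference 0.56 SD: 15–18%.
- Arms pooled, HAMD difference 13.24 − 9.90 = 3.34 points, as in the earlier trial (3.34/4.49 = 0.74 SD): 23–27%.

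Selection on the group difference therefore leaves the within-arm test intact. The inflation appears only when the arms are combined and the score also differs by arm.

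**The case against.** The strongest reply has four parts.

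- **It is a detail for a full plan.** Follow-on correlations are often specified elsewhere, and the article's silence on pooling, time points and change scores is not an error. For those three items this stands. It does not cover the threshold, because the article states the test, the software and the decision rule, and gives correction only to the neighbouring tests.
- **A per-test 0.05 claims only a per-test rate.** This is true: no familywise claim is made for the correlations, and within an arm the per-test rate holds. The point is that no control across the set is offered where several tests are evidently intended.
- **The work is exploratory already.** The first fMRI section does call its overall approach an exploration, but also a robust one that addresses clinical relevance. It does not mark the correlations as hypothesis-generating, and the second section attaches a significance rule to them.
- **The size is assumed.** Region counts appear nowhere, the plan does not say that all four scales will be used, and independence is unlikely. All of this stands, which is why only a range is given.

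A reader might also infer that choosing regions because they were significant is what creates the false links. The documents do not support that. That the correlated regions are the significant ones is itself inferred from adjacent sentences, and step 4 of the working shows that such selection leaves the within-arm error at about 5%.

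**Conclusion.** The point holds as a matter of multiplicity. In both fMRI sections correction is attached to the group or network comparisons, and the correlations with scale scores have none; the second section gives them a bare p < 0.05. With independent tests, the chance of at least one false link is about 14% for 3 regions with HAMD only, 23–40% for 5–10 regions with HAMD only, and 46–87% for 3–10 regions with four scales. It is lower if the tests are correlated.

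The pooling problem is conditional. It needs the arms to be combined and both measures to differ by arm, and then gives about 10–17% per test under the stated assumptions. The 0.56 SD is a planning value from a trial of Tuina against conventional rehabilitation. The comparator here is CBT, and the abstract calls the trial non-inferiority, so the true difference may be smaller and the induced correlation with it.

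Two stronger readings go too far. The 87% is not the plan's error rate; it is the result for an assumed 10 regions, all four scales and independence. Nor do the documents say that a significant correlation will be reported as proof of mechanism; they only leave that open. The primary HAMD comparison and its sample size are not touched.

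**What to change.** In both fMRI analysis sections:

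- State that FDR control extends over all region-by-scale correlations, or name a small number of region–scale pairs in advance and correct over those.
- Correlate change in the brain measure with change in the scale, by partial correlation adjusted for arm or separately within each arm.
- Label these results exploratory.

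The cost is analysis-plan wording and fewer correlations reaching significance. No additional patients, visits or scans are needed.

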## Discussion

PSD is a common and disabling condition that significantly impacts the rehabilitation outcomes of stroke survivors. It is characterized by a complex interplay of biological, psychological, and social factors, making its management challenging. Although there have been advances in drug and psychological treatments, many PSD patients still do not respond well to current therapies, showing the need to explore alternative and complementary methods. As a traditional Chinese medicine therapy, Tuina can effectively alleviate depression and improve cognitive function in PSD patients by activating the hippocampus and regulating brain functional connections (20). In recent years, rTMS, as a non-invasive brain stimulation technique, has also shown promise in modulating cortical excitability and improving mood in depressive disorders (28). This approach combines the holistic benefits of TCM with the precise neurophysiological effects of TMS, offering an innovative treatment strategy.

The pathogenesis of PSD is relatively complex. Structural magnetic resonance imaging and fMRI can reflect changes in brain morphology and function, and can be used for visualizing unknown brain lesions in psychiatric and neurological disorders (29). Dysfunction in functional brain networks may play a critical role in the development of PSD (30). Studies have shown significant reorganization of functional brain networks in PSD patients (31). First introduced by Raichle (32), the concept of the DMN identifies the precuneus and posterior cingulate cortex as key nodes within this network. These regions exhibit significantly higher metabolic activity during the resting state compared to other brain areas (33). Additionally, disruptions in the functional connectivity of the default mode network, which are closely associated with emotional regulation, have been linked to the severity of PSD symptoms (34). Research has demonstrated that reduced FC in the precuneus, posterior cingulate cortex, and angular gyrus of the DMN significantly correlates with anxiety and depression scores in patients (35). Moreover, the pathological changes in PSD are also closely related to the limbic system-cortico-striato-pallido-thalamo-cortical circuit (36), which plays a fundamental role in emotional regulation and neuroplasticity. Evidence suggests that massage therapy can activate the hippocampus and insula, promoting functional remodeling of the limbic system, thereby improving emotional and cognitive functions (37, 38). fNIRS is characterized by its non-invasive nature, portability, and high safety profile, making it well-suited for real-time monitoring of cortical activity in clinical and research settings. By monitoring oxygen metabolism changes in specific cortical regions, it can identify functional abnormalities in key brain areas related to emotional regulation and cognitive function, such as the prefrontal cortex and limbic system, and evaluate the modulatory effects of interventions on brain functional networks (39). Studies have shown that changes in internal and external environments can activate the HPA axis, and dysregulation of the HPA axis is closely associated with the pathogenesis of PSD (40). Approximately 40% of stroke patients exhibit HPA axis hyperactivity, characterized by elevated glucocorticoid levels and hypercortisolism (41). This study uses advanced neuroimaging and biochemical methods to explore the neural mechanisms of PSD and assess the impact of intervention. Investigating the characteristics and remodeling patterns of functional brain networks following Tuina combined with rTMS intervention can help identify activated brain regions and associated neural circuits.

The significance of this study lies in its potential to provide robust evidence on the combined effects of Tuina and TMS for treating PSD. By evaluating both clinical outcomes, such as depressive symptoms and functional recovery, and neurophysiological mechanisms through advanced imaging and biomarker analyses, this research aims to bridge the gap between traditional therapies and modern neuroscience. It also seeks to establish a standardized protocol for the combined intervention, contributing to the evidence base for integrative medicine in stroke rehabilitation.

Our clinical study also has some limitations. First, as the intervention is a non-pharmacological treatment, implementing a double-blind design is challenging, which may introduce potential bias. To address this limitation, we ensured that outcome assessors and data analysts remain blinded throughout the trial. In addition, participants in both groups receive consistent instructions and equal levels of therapist contact, with matched treatment frequency and duration. These measures are intended to reduce expectation-related bias and help account for nonspecific intervention effects. Second, the sample size, although the sample size is relatively modest and may limit the generalizability of the findings to broader populations, it was carefully calculated based on effect size estimates from previous studies and includes a buffer for potential dropout. Participants were recruited from multiple clinical departments within a tertiary hospital and nearby community health centers, which we believe captures a diverse and representative PSD population. These design choices aim to balance statistical rigor with practical feasibility, thereby enhancing both the internal validity and real-world relevance of the study. Moreover, variations in individual patient responsiveness to TMS or massage due to underlying neurobiological or psychological factors may also affect the generalizability of the results. Patients’ expectations regarding the effectiveness of treatment should also be considered in future research.
